## 5 Data storage and record keeping

All information collected from study participants will be treated as strictly confidential and accessibly by study personnel only. Data will be stored in a restricted-access building at TTH and then sent to Menzies School of Health Research in a locked filing cabinet or password-protected electronic database. Study participants will be issued with a numerical code and will not be identifiable in any publications. Data will be stored for 15 years or until the child reaches the age of 25 (whichever is greater).

Samples to be used for research purposes (nasopharyngeal swab and nasopharyngeal aspirate) will be processed and stored in the restricted-access PC2 laboratory of Menzies School of Health Research by trained study personnel. Samples sent to the QPID laboratory for analysis will be transported by courier and will be identified by numerical code only.

## 6 Quality control/quality assurance

This study will be conducted in accordance with the NHMRC Guidelines on Ethical Matters in Aboriginal and Torres Strait Islander Health Research, the Note for Guidance on Good Clinical Practice and the Declaration of Helsinki. Ethics approval and Clinical Trial Protocol committee reviews for the protocols and subsequent amendments will be sought prior to implementation.

Adequately trained and experienced personnel will be employed for trial related activities. This will be documented by way Curriculum Vitae to be kept at Menzies School of Health Research.

### 6.1 Safety parameters

Safety profile, as measured by the incidence, intensity, and relationship to study drug of adverse events and serious adverse events.

An **adverse event** is any untoward medical occurrence experienced by the participant while undergoing treatment in a clinical trial, and up to one week after the dose of Study medicine. Adverse events include temporary, moderate discomfort and disability to the participant.

A **serious adverse event** is defined as any event that is fatal or life threatening is permanently disabling to the participant, any admission to hospital, or an overdose that requires additional medical management

### 6.2 Methods of assessing safety parameters

Side effects of Azithromycin are rare. Those listed in MIMS Annual 2001 included: nausea, vomiting, diarrhoea, or abdominal pain. Rare but potentially serious side effects listed are angioedema and cholestatic jaundice.

The children enrolled in the study have been admitted to TTH and RDH and as such are monitored according to hospital protocol. The child's progress is monitored daily by the study staff via the medical chart and the Nursing Unit Manager.

### 6.3 Flowchart – adverse event reporting

[figure not shown]

#### 6.4 Classification and reporting of serious adverse events

All SAEs will be investigated and assessed to determine whether the event was caused by administration of a study medicine. Causality will be assessed against the definitions below, which are based on standard WHO criteria.

| Classification           | Definition                                                                                                                                                                                                     | Report to Safety Monitor |
|---------------------------------|-----------------------------------------------------------------------------------------------------------------------------------------------------------------------------------------------------------------------|---------------------------------|
| Very likely/
Certain | A clinical event with a plausible time relationship to medication administration/non-administration and which cannot be explained by concurrent disease or other drugs or chemicals                                   | Within 24 hours          |
| Probable                 | A clinical event with a reasonable time relationship to medicine administration/non-administration; is unlikely to be attributed to concurrent disease or other drugs or chemicals                                    | Within 24 hours          |
| Possible                 | A clinical event with a reasonable time relationship to medicine administration/non-administration, but which could also be explained by concurrent disease or other drugs or chemicals                               | Within 24 hours          |
| Unlikely                 | A clinical event whose time relationship to medicine administration/non-administration makes a causal connection improbable, but which could plausibly be explained by underlying disease or other drugs or chemicals | Within 30 days           |
| Unrelated                | A clinical event with an incompatible time relationship and which could be explained by underlying disease or other drugs or chemicals                                                                                | Within 30 days           |
| Unclassifiable           | A clinical event with insufficient information to permit assessment and identification of the cause                                                                                                                   | Within 30 days           |

All SAEs will be investigated by the Chief Investigator in consultation with the Independent Safety Monitor. Causality will be assigned using the above definitions. The findings of each investigation will be reported to the Independent Safety Monitor within the time periods specified above in a standard format (see SAE Brief Case Summary).

SAEs with a causality classification of “very likely/certain”, “probable” or “possible” must also be reported to the Chief Investigator and Chair of the DSMB within 24 hours of the determination. The reports will consist of line listed data showing participant identification number, community, randomisation date, age, group allocation, diagnosis of SAE, causality of SAE, outcome of SAE, continuation/withdrawal from study. Other causality classifications will be reported to the DSMB in summary format within 30 days.

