#### 4.2.2 Randomisation and blinding of treatment allocation

This is a double-blind, randomised, placebo-controlled trial with concealed allocation. The study medications will be assigned the labels A, B, C or D (two labels assigned to placebo azithromycin and two assigned to azithromycin) by an independent person of the study at Menzies School of Health Research. Neither the study team (researchers, hospital staff) nor parents will know which treatment group (placebo or azithromycin) the infant has been assigned until the results have been analysed. Placebo azithromycin has been specifically manufactured by IDT Australia Limited (Melbourne, Victoria) and has a similar smell and taste to active azithromycin. The manufacture of placebo was

primarily for our NHMRC funded international study on bronchiectasis in Indigenous children.

The treatment allocation list has been computer generated by using stratified block randomisation. There are 4 sheets, each corresponding to the treatment strata. Treatment allocation has been concealed by black sticker. Upon enrolment an infant will be assigned to the next treatment on the appropriate stratified list and the treatment (A, B, C or D) revealed.

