**Procedure:**

1. After identifying the correct strata write the child's name and HRN on the next available line. The number refers to the child's study identification number.
2. Remove the sticker to reveal the study medication allocation (letter A, B, C or D). Record this on the child's chart notification sticker and on the enrolment form.
3. Treating physician to complete ABIS script to order medication/placebo on medication chart (dose 30mg/kg). Medication scripts are found in the study documents and are given to physician by ABIS study staff.
4. ABIS script taken to pharmacy by ABIS study staff and medication dispensed.
5. Take medication back to the paediatric ward and inform the nurse looking after the child that the child has been enrolled in the study.
6. For children enrolled on the weekends, please ensure that scripts are taken down to the Pharmacy before 1000hrs to ensure the pharmacy has enough time to dispense. Administer/supervise administration of first dose of medication.

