#### **4.3 Study size**

We plan to enrol 100 infants total. Children will be stratified by age (6 months and less and over 6 months), Indigenous status (Indigenous and non Indigenous) and site (Darwin and Townsville). The mean length of stay for bronchiolitis at Royal Darwin Hospital is 96 hours. To detect a mean difference of 24 hours in length of stay between treatment groups with an alpha of 0.05 and a power of 90%, the required sample size is 23 infants per group.

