### **6.5 DSMB (Data Safety Monitoring Board)**

The DSMB is an independent group of experts that advises the study investigators. The members of the DSMB serve in an individual capacity and provide their expertise and recommendations to guide the clinical trial. An elected member of the DSMB will become the independent safety monitor of the study.

The DSMB, unblinded, will review all events (i.e. mild, moderate, severe or life-threatening events), whether they are related or unrelated to the administration of study drug. The DSMB will meet in person or via telephone link up at the start of the trial and on a six-monthly basis after that. The DSMB will also review any Serious Adverse Event in an expeditious manner as they are reported.

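### The SAE report in section 6.4 gives the Chief Investigator the group allocation, in conflict with the blinding in 4.2.2; with four shared letters, one report can reveal about a quarter of the infants

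*Protocol*

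**What the plan says.** Section 4.2.2 describes a double-blind trial: "Neither the study team (researchers, hospital staff) nor parents will know which treatment group (placebo or azithromycin) the infant has been assigned", and this holds until the results have been analysed. On coding, the same section says: "The study medications will be assigned the labels A, B, C or D (two labels assigned to placebo azithromycin and two assigned to azithromycin". The procedure that follows has staff uncover the infant's letter at enrolment, with the instruction: "Record this on the child's chart notification sticker and on the enrolment form".

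Section 6.4 makes the Chief Investigator responsible for assessing events: "All SAEs will be investigated by the Chief Investigator in consultation with the Independent Safety Monitor". SAEs whose causality is rated possible, probable or very likely/certain "must also be reported to the Chief Investigator and Chair of the DSMB within 24 hours of the determination". The content of these reports is then fixed: "The reports will consist of line listed data showing participant identification number, community, randomisation date, age, group allocation, diagnosis of SAE", followed by causality, outcome and study status. One format is given for both recipients. The remaining causality classes go to the DSMB in summary form.

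Section 6.5 states the blinding status of one body only: "The DSMB, unblinded, will review all events". Section 4.3 gives the planned size: "We plan to enrol 100 infants total".

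**The concern.** The Chief Investigator is part of the study team that 4.2.2 keeps blind, yet is a named recipient of a listing that includes allocation. If that item is the arm, the two sections cannot both be followed.

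The coding scheme widens the effect. With a separate code for each infant, disclosing one allocation would unblind one infant. Here the letter is common to many infants and stands in each chart and on each enrolment form. Linking one letter to an arm therefore identifies every infant with that letter, whether already enrolled or still to come.

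Two things are at stake. The Chief Investigator investigates every SAE, so later causality ratings could be made with knowledge of the arm. In addition, the primary outcome (length of stay, 4.8.1) and the oxygen outcome (4.8.2) depend partly on ward judgement; the acute end-point in 4.6, for example, includes how well the infant is feeding. If knowledge of a letter reached the people making those judgements, the outcomes could be affected.

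**Working it through.** The protocol gives no figure for unblinding, so there is none to reproduce. The check compares the sections and then counts how far one disclosure spreads.

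**Comparing the sections**

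| Question | Section | Answer |
|---|---|---|
| Who must stay blind to arm? | 4.2.2 | The study team and parents, until the results have been analysed |
| Who is described as unblinded? | 6.5 | The DSMB |
| Who receives the listing? | 6.4 | The Chief Investigator and the DSMB Chair |
| Does the listing include allocation? | 6.4 | Yes, with no separate version for the Chief Investigator |

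The Chief Investigator investigates each SAE and so should already hold most of the other items in the listing. If allocation means the arm, it is the item that would be new.

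**How far one disclosure spreads**

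Inputs: 100 infants (4.3); 4 letters, 2 per arm (4.2.2). Assumption: the letters are used equally. Section 4.2.2 specifies stratified block randomisation but gives no ratio between letters.

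- *Infants per letter:* 100 / 4 = 25. The first report that pairs a letter with an arm reveals 25 of 100 infants.
- *Remaining infants after one report:* of the other three letters, two belong to the opposite arm. Guessing the opposite arm for them is right 2/3 of the time. Over the whole trial the best guess is right for 0.25 + 0.75 × 2/3 = 0.75 of infants, against 0.50 under blinding.
- *Both letters of one arm known:* the other two letters must belong to the other arm, so all 100 infants are revealed. Any three letters necessarily include such a pair.

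**Several reports**

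Suppose k reports concern infants whose letters are independent and equally likely. There are 4^k letter sequences. The blind is not wholly lost only if the sequence has at most one letter from each arm, which happens in 4 × 2^k − 4 sequences: 4 of these use a single letter (25% revealed) and the rest use two letters from opposite arms (50% revealed). Hence P(all revealed) = 1 − (4 × 2^k − 4) / 4^k.

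| Reports k | Sequences: one letter / two opposite / all revealed | Expected share revealed | P(all 100 revealed) |
|---|---|---|---|
| 1 | 4 / 0 / 0 of 4 | 25% | 0% |
| 2 | 4 / 8 / 4 of 16 | (1 + 4 + 4)/16 = 56% | 4/16 = 25% |
| 3 | 4 / 24 / 36 of 64 | (1 + 12 + 36)/64 = 77% | 36/64 = 56% |
| 4 | 4 / 56 / 196 of 256 | (1 + 28 + 196)/256 = 88% | 196/256 = 77% |

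If qualifying events fell mainly in one arm, the spread would be faster: two reports from the same arm carry different letters with probability 1/2, and that reveals everything.

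These results are conditional on k. The protocol gives no basis for estimating k.

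**The case against.** The strongest objection is that the allocation item is not defined. The enrolment procedure in 4.2.2 also uses the word allocation for the letter uncovered beneath the sticker. The labels were assigned by an independent person, and nothing in the text describes the code being broken for an SAE report. If the listing shows only the letter, it adds nothing to what is already in the chart, and nobody is unblinded. The flow chart in 6.3 and the case summary form cited in 6.4 are not available to read and might settle the point. This stands as a reason not to say that the plan certainly unblinds the Chief Investigator. It does not remove the problem: 4.2.2 uses treatment group to mean placebo or azithromycin, and the other recipient belongs to an unblinded board. Both favour reading the item as the arm, and the blind should not depend on which reading staff adopt.

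Four stronger inferences are tempting, but the document does not support them:

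- *That the listing biases the rating of the event it reports.* It is sent after causality has been determined, so only later events could be affected.
- *That length of stay and oxygen time are biased.* Section 4.6 leaves care to hospital staff under standard practice, and the listing goes only to the Chief Investigator and the DSMB Chair. Bias requires the knowledge to travel further. The protocol states no barrier to that, but does not show it happening.
- *That six-month readmissions would generate many unblinding reports*, because 6.1 counts any hospital admission as serious. Only events rated possible or higher go to the Chief Investigator, 6.1 limits adverse events to one week after the dose, and nothing suggests that a late readmission would be rated possible.
- *That concealment of later allocations is lost.* The next letter stays covered until enrolment, so knowing what a letter means does not show which letter comes next.

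It is also fair to say that two letters per arm is a deliberate masking device. It is weaker than individual codes, but it is not an error in itself.

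**Conclusion.** The concern holds in a limited form. Sections 4.2.2 and 6.4 conflict on the more natural reading of 6.4, and are ambiguous on the other. If the item is the arm, the first report reveals about 25 of 100 infants and lifts the best guess over the whole trial from 50% to 75% correct; reports covering both letters of one arm reveal everyone. The figure of 25 assumes equal use of the letters and applies per disclosure. It is not an expected loss for the trial, because the number of SAEs rated possible or higher is not given and may be small or zero.

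The direct risk is to the Chief Investigator's causality assessment of later events. Effects on length of stay and time on oxygen are possible only if the knowledge reaches ward staff. The correction is still worth making before any such report is sent, because a disclosed letter cannot be made blind again.

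**What to change.** In section 6.4, remove allocation from the report sent to the Chief Investigator, and state that it goes only in a closed copy to the unblinded DSMB Chair. The same sentence should say whether the item means the arm or the letter. The cost is one sentence in an amendment, plus the ethics review that section 6 requires for amendments. No safety oversight is lost, since the DSMB still receives the allocation.

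Optionally, replace the four shared letters with a medication number unique to each infant, so that any unblinding, by this or another route, affects one infant only. This would need relabelled medication and new allocation lists in place of those already generated, at two sites. It is not needed to resolve the conflict between the two sections.

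### Unclassifiable SAEs take the 30-day route to the DSMB, the Chair's 24-hour clock starts only at a causality determination, and prolonged stay is not a seriousness criterion

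*Protocol*

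**What the plan says.** Protocol section 6.1 defines a serious adverse event as "any event that is fatal or life threatening is permanently disabling to the participant, any admission to hospital", together with an overdose needing additional management. Prolongation of an existing hospital stay is not on the list. The same section limits adverse events to the treatment period "and up to one week after the dose of Study medicine" and does not say whether that limit also applies to serious events.

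Section 6.2 confirms the setting: "The children enrolled in the study have been admitted to TTH and RDH and as such are monitored according to hospital protocol".

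Section 6.4 sets reporting times by causality class. Very likely/certain, probable and possible SAEs have a 24-hour limit to the Independent Safety Monitor. They "must also be reported to the Chief Investigator and Chair of the DSMB within 24 hours of the determination". Unlikely, unrelated and unclassifiable SAEs have 30 days to the Safety Monitor, and for the DSMB the rule is: "Other causality classifications will be reported to the DSMB in summary format within 30 days". An unclassifiable event is defined as "A clinical event with insufficient information to permit assessment and identification of the cause".

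Section 6.5 has the unblinded DSMB review all events at six-monthly meetings, whatever their severity or relatedness, and adds: "The DSMB will also review any Serious Adverse Event in an expeditious manner as they are reported".

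**The concern.** A causality class is a judgement made after the event, and here it controls how fast the DSMB is told. This causes three difficulties.

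- An event whose cause cannot be assessed has not been cleared of a link to study drug, yet it travels with events judged unlikely or unrelated.
- The rapid report to the Chair is tied to the end of the causality assessment. A slow assessment therefore delays the report even for an event later judged certain.
- The admission criterion does little for infants who are already in hospital when dosed. Extension of the current stay is the natural counterpart of admission for an inpatient, and it is missing.

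At stake is the timeliness of safety oversight in infants aged 18 months or less. No efficacy analysis, sample size or estimate is affected.

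**Working it through.** The plan gives no statistical figure to reproduce. The check compares sections 6.1 to 6.6 and converts the stated time limits.

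**1. Routes by causality class (section 6.4)**

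| Class | Limit to Safety Monitor | Route to DSMB |
|---|---|---|
| Very likely/certain, probable, possible | 24 hours | Chair, within 24 hours of the determination |
| Unlikely, unrelated | 30 days | Summary, 30 days |
| Unclassifiable | 30 days | Summary, 30 days |

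Three of the six classes take the slow route. For unlikely and unrelated events, someone has judged the drug an improbable cause. For unclassifiable events, nobody could judge. Nothing in section 6.4 takes deaths or life-threatening events out of that row.

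**2. Size of the slow limit**

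- 30 days × 24 hours = 720 hours.
- Against the rapid limit: 720 / 24 = 30 times as long.
- Against the mean stay of 96 hours in section 4.3: 720 / 96 = 7.5 mean stays.

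The text does not say when the 30 days start. If they start at the event, 720 hours is the maximum. If they start at classification, the time taken to classify is added.

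**3. The Chair's clock**

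Time from event to the Chair's report = time to causality determination + up to 24 hours. The first term has no limit in the visible text, so the sum has none either. For the Safety Monitor, section 6.4 times the findings of the investigation and gives no starting point.

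**4. Fit with section 6.5**

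Section 6.5 covers any SAE, but review begins only once a report arrives. For half of the classes, section 6.4 allows the report to arrive as a summary up to 30 days later. Prompt review of any SAE cannot be assured under that rule.

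**5. Seriousness criteria applied to an inpatient**

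Consider an in-hospital reaction that is neither fatal nor life threatening, causes no permanent disability, is not an overdose, and keeps the infant in hospital longer. Under section 6.1 it meets no criterion: the admission has already happened, and extension is not listed. It is an adverse event only. Section 6.2 itself names angioedema and cholestatic jaundice as potentially serious effects, and either could take this form. The visible text gives such an event one stated route to the DSMB, the six-monthly review, so the wait can be up to about six months.

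**6. Readmissions**

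Readmission within 6 months is a secondary outcome (section 4.8.2) and also matches "any admission to hospital, or an overdose that requires additional medical management". If the one-week window applies to SAEs, only first-week readmissions are serious events. If it does not, every readmission is. Section 6.1 does not say which.

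**The case against.** The best defence is that the DSMB is better informed than section 6.4 suggests on its own.

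- **The Safety Monitor.** This person is a voting DSMB member and the main DSMB contact for SAEs (section 6.6), and is consulted in the investigation of every SAE whatever its class (section 6.4). One DSMB member may therefore know of an event before causality is assigned. This stands, and the 30-day report need not be the DSMB's first knowledge of an unexplained death. However, the visible text sets no time for that first contact.
- **Review of all events.** A reader might infer that stay-prolonging reactions never reach the DSMB. The documents do not support that. Section 6.5 covers all events of any severity, and study staff follow each child daily (section 6.2). An event recorded as an adverse event would be seen, possibly late.
- **What counts as serious already.** Fatal, life-threatening and permanently disabling in-hospital reactions are SAEs under section 6.1. The definition gap concerns only other reactions.
- **The flow chart.** Section 6.3 is a reporting flow chart that is not shown, and the SAE case summary form named in section 6.4 is not shown either. Either may hold an initial notification time, so its absence from the whole plan cannot be asserted. Such a time would settle the clock, but it would not by itself change the 30-day rule for unclassifiable events or the SAE definition.
- **Overlap with the primary outcome.** Length of stay is compared between arms, so prolongation is measured. That is a group comparison of the outcome and does not alert the DSMB to an individual event. The overlap does mean that any new criterion must separate an adverse reaction from slow recovery.

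**Conclusion.** The point holds as a reporting weakness that should be amended. Three elements are firm on the visible text:

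- unclassifiable SAEs share a 30-day summary route, 30 times the rapid limit;
- the Chair's 24-hour report runs from a determination with no visible deadline;
- prolongation of the current stay is not a seriousness criterion, so a non-life-threatening, non-disabling reaction that extends it may wait for the next six-monthly review.

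The first two do not fit the promise of expeditious review in section 6.5. The second depends on the section 6.3 flow chart not setting an earlier notification time. The third assumes that the event is recorded as an adverse event at all.

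A reader might also infer that readmissions will flood SAE reporting, given the 30% six-month readmission rate quoted for Indigenous children in section 3.4.1. The documents do not support that. The number of Indigenous infants to be enrolled is not given, and the one-week window may exclude most readmissions. Readmissions judged unlikely or unrelated would not use the 24-hour route in any case. What can be said is that section 6.1 leaves the handling of later readmissions unclear.

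**What to change.** First check the section 6.3 flow chart for an initial notification time. Then amend sections 6.1 and 6.4 and the SAE form:

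1. Move unclassifiable SAEs into the 24-hour group.
2. Run the 24-hour report to the Safety Monitor and the DSMB Chair from the time staff become aware of the event, with a provisional causality class that is updated later. If the flow chart already sets such a time, repeat it in section 6.4.
3. Add to the SAE definition prolongation of the current stay that is attributed to an adverse event, and exclude prolongation due to slow recovery from bronchiolitis.
4. State whether the one-week adverse event window also applies to SAEs, so that later readmissions are handled as the secondary outcome and tabulated for the six-monthly DSMB review.
5. Align the wording of section 6.5 with the amended section 6.4.

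The cost is one amendment, a revised form and a few more rapid reports. Staff must also judge, case by case, whether a longer stay reflects an adverse event or the illness itself. Sample size and efficacy analysis do not change.
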